#### State-Trait Anxiety Inventory

The STAI (Spielberger et al., 1983) is the most widely used screening tool to identify anxiety in pregnancy (Brunton et al., 2015). It is a self-rating scale containing 40 items divided into two subscales of 20 items each, which evaluate different types of anxiety: the state subscale measures anxiety in the current situation or time period, while the trait subscale measures relatively stable individual aspects of propensity toward elevated anxiety. The answer to each item is on a four-point Likert scale. The total score ranges from 20 to 80, with higher scores indicating more severe anxiety. The STAI internal consistency ranged from 0.86 to 0.95 (Spielberger et al., 1983; Spielberger, 1989) and the Italian version (Pedrabissi and Santinello, 1992) showed psychometric properties consistent with the English version. The adopted cut-off score was ≥ 40, as suggested by the STAI Italian version (Pedrabissi and Santinello, 1992), validated on a non-pregnant population. The construct and content validity of the STAI for pregnant woman has been proven (Gunning et al., 2010). The sensitivity, specificity, and positive predictive value of the STAI for the third trimester of pregnancy were recorded as 80.95, 79.75, and 51.50%, respectively, based on a cut-off score of >40 for both state and trait scales (Grant et al., 2008). A cut-off score of >40 for the postpartum period is recommended (Dennis et al., 2013). The state scale of the STAI is strongly correlated with the EPDS (Meades and Ayers, 2011).

#### Psychosocial and Clinical Assessment Form

The Psychosocial and Clinical Assessment Form (Palumbo et al., 2016) is developed by the Italian National Institute of Health. There are two questionnaires: a pregnancy and a postnatal version. The pregnancy version is composed of 22 items addressing sociodemographic characteristics, information on mental health before pregnancy, stressful life events experienced over the last twelve months, information about the pregnancy and currently perceived family and social support. Whereas the postnatal version has an additional seven items to gather information on childbirth. The resulting psychosocial and clinical risks and protective factors can be weighted and summarized into two different psychological constructs: (a) perceived confidence in personal abilities and own social resources, and (b) perceived psychological vulnerability and ability to cope with the difficulties.

#### Italian Questionnaires of Temperament

The QUIT (Axia, 2002) is a set of questionnaires that are used to measure temperament in infants from the first month up to 11 years of age. This study uses the QUIT 1–12 and 12–36 month Scales. It is a caregiver-report questionnaire validated with reference to Italian culture, containing 55 items investigating six dimensions: attention, inhibition to novelty, motor activities, positive emotionality, negative emotionality and social orientation. The first three dimensions relate to adaptation in general, while the second three relate to specific adaptation to the social world. The answer to each item is on a six-point Likert scale with which mothers indicate their baby’s positive or negative attitude toward the environment, with higher scores indicating greater intensity of a characteristic. Four infant temperamental profiles can be obtained on the basis of the orthogonal dimensions of positive and negative emotionality: emotional temperament, calm temperament, normal temperament, difficult temperament. The QUIT has acceptable internal consistency with Cronbach’s alpha ranging from 0.59 to 0.71 (Axia, 2002), and the Pearson’s correlation coefficient among reports by mothers and fathers ranges from 0.32 to 0.62 (Axia and Weisner, 2002).

#### World Health Organization Quality of Life BREF

The WHOQOL-BRIEF (The Whoqol Group, 1998) is a generic instrument to assess perceived quality of life (QoL). It is a self-rating questionnaire containing 28 items, of which 26 are used to measure four domains related to QoL: physical health, psychological, social relationships and environment. A further two items are used to measure individual perceptions of overall QoL and general health. The answer to each item is on a five-point Likert scale with which mothers indicate their degree of satisfaction/dissatisfaction. Domain scores are calculated by multiplying the mean score of all items within each domain by four and then they are transformed into weighted scores from 0 to 100, with higher scores indicating greater levels of satisfaction. There is no an overall score. The WHOQOL-BRIEF Italian version showed good internal consistency, with Cronbach’s alpha ranging from 0.65 for the social relationships domain to 0.80 for the physical domain (de Girolamo et al., 2000). The WHOQOL-BREF is widely used to measure the QoL of women during the perinatal period (Webster et al., 2010; Nascimento et al., 2011; Mortazavi et al., 2014; Moura et al., 2017).

#### Mini-International Neuropsychiatric Interview-Plus

The MINI-Plus (Sheehan et al., 1998) is a short, structured and standardized diagnostic interview developed to assess the diagnosis of psychotic and mood disorders based on DSM-IV criteria. Its sensitivity, specificity, and reliability are equivalent to those of the Structured Clinical Interview for DSM-IV in different settings (psychiatric and primary care centers) (Sheehan et al., 1998; Amorim, 2000). This study uses the module for depressive disorders, which addresses the frequency, intensity, and duration of depressive symptoms and the degree of the associated distress and impairment. For major depressive disorders, the interrater reliability of the MINI Italian version was 0.96 (Rossi et al., 2004), indicating “excellent agreement.”

### Sample Size

Assuming 10–15% prevalence of perinatal depression as measured by EPDS (Gavin et al., 2005; Melville et al., 2010) the minimum number needed of mothers to be screened is 500.

With regard to the clinical trial on the psychological interventions for perinatal depression and anxiety, the power calculation was based on detecting an effect size of medium magnitude (*d* = 0.55) at the follow-ups on the EPDS among the patients (Cohen, 1988). We calculated that a sample size of 45 patients would result in a power of 0.95 with alpha set at 0.05. To protect against an anticipated loss to follow-up of about 30% (Mirabella et al., 2016), we planned to enroll 65 patients.

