#### Phase 5: Follow-up

Changes in the patients’ clinical conditions are re-evaluated at three points of follow-up (end of intervention, 6th month and 12th month) using EPDS, PHQ-9, STAI, WHOQOL-BREF, QUITs, MINI-Plus and a clinical interview.

Mothers who are still depressed after the intervention phase are sent to a clinical psychological or psychiatric service.

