### Study Outcomes

The data on maternal psychosocial and clinical conditions will be gathered. The primary outcomes are maternal depressive and anxiety symptoms severity. Secondary outcomes are maternal perceived quality of life and infants’ temperament (only for the infants whose mothers participated in the intervention).

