### Data Analysis Plan

The prevalence of antenatal and postpartum depression and the risk of anxiety will be calculated and compared. Since previous studies have ascertained a higher risk of developing depression in the postpartum period, the antenatal period will be taken as a reference to calculate the odds ratio as a measure of the relative risk of depression between antenatal and postpartum periods, using chi-square as a test for statistical significance.

The sensitivity, specificity and predictive values of the EPDS and the PHQ-9 versus the MINI will be analyzed. Factors associated with ante- and post-partum depression and anxiety risk will be analyzed using a logistic regression model.

With regard to the effectiveness of treatment, standard descriptive statistics will be calculated for all questionnaires. Analysis of variance for repeated measurements will be performed to compare the differences between each initial score obtained with the different administered questionnaires and the scores at T1 (end of treatment), T2 (after 6 months) and T3 (after 12 months) will be evaluated. Bonferroni *post hoc* comparisons will be conducted. Treatment effect will be calculated using Cohen’s d for each of the follow-up times. The Reliable Change Index will be calculated for each time, in order to determine any significant clinical changes occurring in each individual case post treatment.

Data will be analyzed using the Statistical Package for Social Science (SPSS) for Windows version 22.0.

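### The stated power of 0.95 belongs to one uncorrected paired test; the planned Bonferroni comparisons of EPDS follow-ups have power of about 0.88 or 0.82

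*Protocol article*

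**What the plan says.** The Sample Size section states that "the power calculation was based on detecting an effect size of medium magnitude", with d = 0.55, "at the follow-ups on the EPDS among the patients". It continues: "We calculated that a sample size of 45 patients would result in a power of 0.95 with alpha set at 0.05". It then allows for attrition ("To protect against an anticipated loss to follow-up of about 30" per cent) and concludes that "we planned to enroll 65 patients". It does not mention multiple comparisons, the sidedness of the test, or which standard deviation scales d.

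The Data Analysis Plan applies a repeated-measures ANOVA to each questionnaire over the initial score, T1 (end of treatment), T2 (6 months) and T3 (12 months). It adds that "Bonferroni *post hoc* comparisons will be conducted", and asks for Cohen's d at each follow-up time. It does not say whether the Bonferroni family is the three contrasts with baseline or all six pairs of time points.

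Study Outcomes says: "The primary outcomes are maternal depressive and anxiety symptoms severity". No single scale or time point is named.

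**The concern.** The sample size is justified by an effect at the follow-ups, in the plural. The step that shows whether the EPDS has changed at a particular follow-up is the Bonferroni-corrected comparison, which uses a significance level below 0.05. If the 0.95 was computed at an uncorrected 0.05, the article claims a power that its own analysis does not have for those comparisons. This is not a detail left to a later analysis plan, because the article fixes both the power figure and the correction.

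What is at stake is how a non-significant follow-up result will be read. Under the stated power, the chance of missing the target effect is 5%. Under the planned comparisons it is larger, and a reader relying on the stated figure would take a null result at T2 or T3 as stronger evidence than it is.

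**Working it through.** **Inputs.** From Sample Size: d = 0.55, n = 45 analysed, alpha 0.05, power 0.95, loss 30%, enrolment 65. From the Data Analysis Plan: four time points, giving 3 contrasts with baseline or 4 × 3 / 2 = 6 pairwise contrasts. Assumptions: two-sided tests, and d is the mean paired change divided by the SD of that change.

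**Step 1: reproduce the stated figure.** For a paired t-test, the statistic has a noncentral t distribution with df = n − 1 and noncentrality d√n. Here df = 44 and the noncentrality is 0.55 × √45 = 3.690.
- Two-sided alpha 0.05: critical value 2.015, power 0.9503. The smallest n that reaches 0.95 is 45.
- Alternatives do not give 45: one-sided, power 0.977 and n = 38; normal approximation, power 0.958 and n = 43; two independent groups of 45, power 0.74.
- Attrition: 45 / 0.70 = 64.3, rounded up to 65. This is correct.

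So the arithmetic in Sample Size is sound, and it describes one uncorrected two-sided paired test.

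**Step 2: the same calculation at the Bonferroni level.** Same df and noncentrality, alpha = 0.05 / m.

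| Family | alpha per test | Critical t | Power, n = 45 | n for 0.95 | Enrolled (n / 0.70) |
|---|---|---|---|---|---|
| 1 test | 0.05 | 2.015 | 0.950 | 45 | 65 |
| 3 baseline contrasts | 0.0167 | 2.489 | 0.880 | 57 | 82 |
| 6 pairwise contrasts | 0.0083 | 2.763 | 0.817 | 65 | 93 |

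The chance of missing the target effect at a given follow-up is 1 − 0.880 = 12% or 1 − 0.817 = 18%, against the stated 5%.

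**Step 3: the omnibus ANOVA at 0.05.** Noncentral F with 3 and 3 × 44 = 132 df, noncentrality n × 2 × 0.55² × f. Here f is the sum of squared deviations of the four means when the largest difference is set to 1, and sphericity is assumed.
- Full change at T1 and maintained (f = 0.75): noncentrality 20.42, power 0.974.
- Linear build-up to T3 (f = 5/9): 15.13, power 0.911.
- Least favourable, two means at the midpoint (f = 0.5): 13.61, power 0.877.

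**Step 4: sensitivity to the scaling of d.** If d is divided by the raw-score SD instead, the paired effect is 0.55 / √(2(1 − r)), where r is the pre-post correlation. The article does not give r.

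| r (assumed) | Uncorrected | 3 contrasts | 6 contrasts |
|---|---|---|---|
| 0.3 | 0.86 | 0.73 | 0.64 |
| 0.5 | 0.95 | 0.88 | 0.82 |
| 0.7 | 0.997 | 0.99 | 0.97 |

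**Step 5: type I error across scales, a separate matter.** Take depressive and anxiety severity as four scores (EPDS, PHQ-9, STAI state, STAI trait), each held to 5%. If they are independent, the family-wise error is 1 − 0.95⁴ = 18.5%. With an assumed common correlation of 0.5 to 0.7 it is about 16% to 13%.

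**The case against.** The strongest reply is that the first test in the plan is the omnibus ANOVA, which is uncorrected, and that the Bonferroni step is only post hoc. If the effect appears at T1 and lasts, the omnibus test has power 0.974. Under that same pattern, with an assumed correlation of 0.5 between time points, simulation puts the chance that at least one corrected baseline contrast is significant at 0.98 (family of 3) or 0.96 (family of 6). This stands for that pattern. It does not rescue the general claim: omnibus power falls to 0.911 or 0.877 under other patterns, and is lower without sphericity. An omnibus rejection also does not say which follow-up differs or in which direction. In the same simulation, all three follow-ups are significant with probability only 0.75 or 0.64.

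A second reply is that the definition of d is not given, so 0.88 and 0.82 are conditional. That is fair, and with raw-SD scaling and r = 0.7 there would be no shortfall. But the change-SD reading returns exactly 45, which makes it the likely basis.

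Two stronger readings are tempting, and the document supports neither. A reader might infer that having several primary scales also erodes the 0.95. Power is stated for the EPDS alone and no correction across scales is planned, so additional scales leave EPDS power unchanged. A reader might also multiply four scales by three follow-ups and reach 1 − 0.95¹² = 46% false positives. That treats all twelve tests as uncorrected and independent. With the planned correction and independence, twelve baseline contrasts give 1 − (1 − 0.05/3)¹² = 18%, or 1 − (1 − 0.05/6)¹² = 10%. The Measures section itself reports a strong correlation between STAI state and EPDS. Nor does the article say that success on any one scale would establish effectiveness.

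**Conclusion.** The mismatch is real but moderate. Nothing in Sample Size is miscalculated: 45, 0.95 and 65 all reproduce. The 0.95 simply belongs to a different test from the Bonferroni comparisons that the Data Analysis Plan uses at the follow-ups. For any given EPDS follow-up comparison with 45 completers, power is 0.88 (three contrasts) or 0.82 (six), which is 7 to 13 percentage points below the stated figure and still above 0.80. This rests on two-sided testing and on d being scaled by the SD of the change. The omnibus ANOVA meets 0.95 only if the change comes early and is maintained, or follows a similarly favourable pattern.

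The lack of a stated correction across the depressive and anxiety scales is a lesser, separate point about type I error. The figure is about 19% if four scores are each tested at 5% and are independent, and less with positive correlation. The number of scores is itself an inference, since Study Outcomes names constructs rather than scales.

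**What to change.** Choose one of two routes, and in either case state in Sample Size that the test is two-sided and that d is scaled by the SD of the paired change.

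1. **Restate the power.** Define the Bonferroni family in the Data Analysis Plan (three contrasts with baseline, or all six pairs) and give the per-comparison power as 0.88 or 0.82 with 45 completers.
2. **Name one primary comparison.** Designate a single EPDS contrast at two-sided 0.05, for example baseline to T1, and make the other time points and scales secondary with the Bonferroni step. The 0.95 and the enrolment of 65 then stand. T1 is one option, not a requirement. One argument for it is that the follow-up section says "Mothers who are still depressed after the intervention phase are sent to a clinical psychological or psychiatric service", so T2 and T3 scores may also reflect later care.

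Route 2 also settles the question across scales. Under route 1, add a sentence saying how the depressive and anxiety scales are ranked or corrected.

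The cost is about two sentences and no extra patients. The downside is a less favourable stated power under route 1, or a narrower primary claim under route 2. Keeping 0.95 for every corrected comparison would instead need 57 or 65 completers (82 or 93 enrolled).

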### Quality Control

The healthcare centers enter all the data collected with the instruments during the Assessment into an Excel database, prepared by the ISS (baseline + follow-up). Once the centers have entered all the data collected, each researcher (coordinator of the healthcare centers) performs a detailed quality control assessment. After this assessment by each center, the data is sent to the Observatory of Perinatal Clinical Psychology (coordinating center), which repeats the same checks, to ensure that the final database contain no errors and have no missing data.

### Data Analysis Plan

The prevalence of antenatal and postpartum depression and the risk of anxiety will be calculated and compared. Since previous studies have ascertained a higher risk of developing depression in the postpartum period, the antenatal period will be taken as a reference to calculate the odds ratio as a measure of the relative risk of depression between antenatal and postpartum periods, using chi-square as a test for statistical significance.

The sensitivity, specificity and predictive values of the EPDS and the PHQ-9 versus the MINI will be analyzed. Factors associated with ante- and post-partum depression and anxiety risk will be analyzed using a logistic regression model.

With regard to the effectiveness of treatment, standard descriptive statistics will be calculated for all questionnaires. Analysis of variance for repeated measurements will be performed to compare the differences between each initial score obtained with the different administered questionnaires and the scores at T1 (end of treatment), T2 (after 6 months) and T3 (after 12 months) will be evaluated. Bonferroni *post hoc* comparisons will be conducted. Treatment effect will be calculated using Cohen’s d for each of the follow-up times. The Reliable Change Index will be calculated for each time, in order to determine any significant clinical changes occurring in each individual case post treatment.

Data will be analyzed using the Statistical Package for Social Science (SPSS) for Windows version 22.0.

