The most common perinatal mental disorders in women during pregnancy and postpartum are depressive syndromes and anxiety syndromes: non-psychotic disorders characterized by the specific feelings and thoughts about the parental role (Robinson and Stewart, 2001). The global prevalence of clinically significant maternal perinatal depression ranges from 10 to 20% (Korja et al., 2018; Earls et al., 2019), while the prevalence of perinatal anxiety disorders ranges from 10 to 24% (Dennis et al., 2018; Yeaton-Massey and Herrero, 2019). Furthermore, the comorbidity of mood disorder and anxiety disorder in perinatal women is common (Falah-Hassani et al., 2016), reaching 40% in some studies (Reck et al., 2008; Austin et al., 2010), but often under-diagnosed (Misri and Swift, 2015). In Italy, the few studies carried out to evaluate the prevalence of perinatal depression and anxiety show large variability. Evaluations of maternal perinatal depression and anxiety record ranges of 1.6–26.6% and 6.4–20.5%, respectively (Currò et al., 2009; Mauri et al., 2010; Banti et al., 2011; Girardi et al., 2011; Giardinelli et al., 2012; Elisei et al., 2013; Palumbo et al., 2016; Clavenna et al., 2017; Di Venanzio et al., 2017; Vizzini et al., 2018). The above-mentioned data are influenced by factors such as different screening tools (which have different psychometric properties) and time periods.

Most studies in the literature undertaken by the Italian National Institute of Health and funded by the Ministry of Health – National Centre for Disease Prevention and Control (Palumbo et al., 2016, 2017, 2018) have focused mainly on the effects of maternal postnatal mental health complications. However, more recent studies (Kendig et al., 2017) have examined maternal antenatal and postnatal depression and anxiety, to understand better their short- and long-term effects on both mother and fetus/child (Dunkel Schetter and Tanner, 2012; Suri et al., 2014; Glover, 2015; van der Waerden et al., 2015; Riva Crugnola et al., 2016; Galbally and Lewis, 2017; Field, 2018; Shonkoff et al., 2019).

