### Hypotheses

(1)On the basis of the current literature (Underwood et al., 2016; Okagbue et al., 2017; Hahn-Holbrook et al., 2018), we expect to find a prevalence of perinatal depression within the range of 13–18%, with higher rates during pregnancy than in the first year following childbirth.(2)Based on previous research (Ghaedrahmati et al., 2017; Leach et al., 2017), we assume that the factors associated with a higher risk of perinatal depression and anxiety will include previous history of depression and anxiety, a negative attitude toward a recent previous pregnancy, high-risk pregnancy, young maternal age, limited social support, and financial problems.(3)In accordance with previous studies on screening for antenatal or postnatal depression (Yawn et al., 2009; Zhong et al., 2014; Santos et al., 2016), we expect that both the Edinburgh Postnatal Depression Scale and the Patient Health Questionnaire-9 will be reliable and valid scales for the assessment of perinatal depression.(4)Based on a prior Italian study (Mirabella et al., 2016) showing the effectiveness of Jeannette Milgrom’s (Milgrom et al., 1999) psychological intervention among women suffering from postpartum depression, we assume that intervention can be effective also with antepartum depressed women.(5)Given that the literature (Erickson et al., 2017) has offered ambiguous results on the association between prenatal maternal mental health and the development of infant temperament, we have no specific assumptions to this regard.

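### The antenatal–postpartum odds ratio for depression is to be read as a relative risk, although at the protocol's own prevalences depression is not rare: a minor error of measure and interpretation

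*Protocol article*

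**What the plan says.** The Data Analysis Plan opens the comparison of the two periods with "The prevalence of antenatal and postpartum depression and the risk of anxiety will be calculated and compared". For depression it then fixes the direction of the contrast, "the antenatal period will be taken as a reference to calculate the odds ratio", states how the result is to be read, "the odds ratio as a measure of the relative risk of depression between antenatal and postpartum periods", and names the test, "using chi-square as a test for statistical significance". The relative-risk reading is attached to depression only. For anxiety no effect measure is named in this comparison.

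The protocol gives its expected frequency of depression in several places:

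- Hypotheses: "we expect to find a prevalence of perinatal depression within the range of 13–18" per cent.
- Sample Size: 10–15% on the EPDS, with at least 500 women screened.
- Background: 10–20% worldwide.

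Under Study Design the study is a prospective cohort. Under Phase 2 each woman is screened once, either before or after birth according to the centre.

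**The concern.** The odds ratio and the ratio of prevalences are different quantities. They nearly coincide when the outcome is rare in both groups or when the groups barely differ. An outcome affecting one woman in ten to one in five is not rare, so an odds ratio presented as a relative risk exaggerates the contrast away from 1, whichever period has the higher prevalence.

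The design does not require the approximation. Women are not sampled by whether they are depressed, and the plan already says that the prevalence in each period will be calculated, so the ratio of prevalences can be obtained directly.

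What is at stake is how the period contrast under the first objective is read. A reader told that an odds ratio of 1.47 measures relative risk would take it as 47% more depression, when the two prevalences behind it differ by a factor of 1.38. This distortion does not shrink as the sample grows.

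**Working it through.** The protocol states no odds ratio, no relative risk and no period-specific prevalence, so there is no planned figure to reproduce. The check asks how far apart the two measures would be at the prevalences the protocol quotes.

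**Inputs.** Depression at 13–18% (Hypotheses), 10–15% (Sample Size) and 10–20% (Background). These are overall ranges. Using their ends as the prevalences of the two periods is an assumption, made only to show size.

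**Formulas.** Let p0 be the antenatal prevalence (the reference) and p1 the postpartum prevalence.

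- Odds ratio: OR = [p1/(1 − p1)] / [p0/(1 − p0)]
- Prevalence ratio: PR = p1/p0
- Hence OR/PR = (1 − p0)/(1 − p1)

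**Worked example, 13% antenatal and 18% postpartum.**

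- OR = (0.18/0.82)/(0.13/0.87) = 0.2195/0.1494 = 1.469
- PR = 0.18/0.13 = 1.385
- OR/PR = 0.87/0.82 = 1.061, so the odds ratio is 6.1% above the prevalence ratio.

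**All pairs.**

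| Antenatal v postpartum | Source of range | OR | PR | OR relative to PR |
|---|---|---|---|---|
| 13% v 18% | Hypotheses | 1.47 | 1.38 | +6.1% |
| 10% v 15% | Sample Size | 1.59 | 1.50 | +5.9% |
| 10% v 20% | Background | 2.25 | 2.00 | +12.5% |
| 18% v 13% | Hypotheses, reversed | 0.68 | 0.72 | −5.7% |

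The last row follows the direction of the first hypothesis, which expects depression "with higher rates during pregnancy than in the first year following childbirth". With the antenatal period as reference, that puts both ratios below 1. The odds ratio is then numerically smaller than the prevalence ratio: a 32% reduction would be reported where the prevalences show 28%. The exaggeration is away from 1 in both directions.

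**Comparison with sampling error.** Assume that the 500 screened women divide evenly, 250 to each period, with prevalences of 13% and 18%.

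- SE(log PR) = √[0.87/(250 × 0.13) + 0.82/(250 × 0.18)] = √(0.0268 + 0.0182) = 0.212
- 95% CI for PR: 1.385 × exp(±1.96 × 0.212) = about 0.91 to 2.10

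The distance between 1.38 and 1.47 is small beside that interval.

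**Effect on the test.** The chi-square statistic is computed from the 2×2 table and is the same whichever ratio is reported beside it.

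**The case against.** The strongest case on the other side has four parts.

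- An odds ratio with a chi-square test is a legitimate summary of a 2×2 table, and it matches the logistic regression planned in the same section for associated factors.
- The discrepancy at the expected prevalences is about 6%, far inside sampling error at 500 women, and no p-value changes.
- The illustrative pairs are ends of a range, not expected values for each period.
- The plan already promises both prevalences, so any reader could divide one by the other.

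Most of this stands, and it keeps the point minor. It does not rescue the wording. The plan does not merely report an odds ratio; it says what the odds ratio measures, and that statement is inaccurate at these prevalences. A small known bias that can be avoided by one division is not excused by a wide confidence interval.

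A reader might infer that the problem is worse for anxiety, because the Background says "the prevalence of perinatal anxiety disorders ranges from 10 to 24" per cent. The document does not support that. The relative-risk wording is confined to depression, and no odds ratio is named for the anxiety comparison. If one were used, the ends of the worldwide anxiety range (10% v 24%) would give 2.84 against 2.40, or 18.4% above. On the Italian ranges in the same section the order reverses: the gap is 17.7% for anxiety (6.4% v 20.5%) and 34.1% for depression (1.6% v 26.6%). Nor does the protocol plan to set the depression contrast against the anxiety contrast.

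A reader might also say that the odds ratio always overstates the ratio. That is true numerically only if depression is commoner postpartum. The plan's rationale that "previous studies have ascertained a higher risk of developing depression in the postpartum period" points that way and the first hypothesis points the other. That disagreement is a separate matter, and settling it would not cure this one.

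**Conclusion.** Wrong as written, for depression only, and minor. The odds ratio lies further from 1 than the ratio of prevalences at every pair examined: by about 6% at the prevalences the protocol expects, and by 12.5% at the extremes of its worldwide range. These sizes rest on treating the ends of quoted ranges as the two period prevalences. If the periods turn out closer together, the gap will be smaller. That the odds ratio is the more extreme of the two does not depend on this assumption; it holds whenever the prevalences differ. The validity of the chi-square comparison is not in question, and no finding is made about anxiety.

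**What to change.** In the Data Analysis Plan, replace the odds ratio read as a relative risk with the prevalence ratio and the prevalence difference for depression between the antenatal and postpartum periods. Take both from the 2×2 table and give each a 95% confidence interval. Keep the chi-square test. If an odds ratio is also reported, label it as an odds ratio and do not interpret it as a relative risk.

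The cost is a change of wording. It needs no new data and no extra participants. The only downside is that the reported contrast will look slightly less striking.
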